### Trial settings

There are four trial centres involving the orthoptic departments of the Queen’s Medical Centre at Nottingham, Southampton General Hospital, The Royal Stoke University Hospital and Moorfields Eye Hospital in London. Patients will be recruited from these centres but the treatment itself is home based.

### Study procedures

#### Screening and eligibility assessments

Potential participants are identified from patients attending the orthoptic departments of participating centres. Aids to recruitment including displaying of posters in these departments and there is a website describing the project that is publically accessible.

### Consent

Consent is taken by the research orthoptists at the trial sites from the participant’s parents or guardians. The opportunity is given also to each participant to provide their assent. Separate parent (Additional file 1) and participant (Additional file 5) information sheets are provided and separate consent (Additional file 2) and assent  (Additional files 3 and 6) forms.

### Baseline assessments

A full orthoptic assessment is performed at baseline and will include:Refractive errorVisual acuityOcular motility and convergence statusPrism Cover Test for horizontal and vertical deviation for near and distanceCover testBinocularity status (including stereoacuity)Fundal check (if not recorded in the hospital record)Quality of life measurement using the CHU-9D.

Visual acuity will be measured by one of Keeler LogMAR crowded, crowded LogMAR Kays pictures or the Bailey-Lovie LogMAR test depending upon the child and the same test will be used throughout for each participant. The amblyopic eye is always tested first and terminates when the participant fails to correctly score 3 out of 4 on a line. The participant is allowed one attempt to correct any error. The vision is scored as the line that the tested was completed on and 0.025 is subtracted for every error made on that line and on the preceding line.

Stereoacuity will be measured both by the pre-school Randot test, so as to be comparable with data from the PEDIG trials [16], and by the tablet-based Game Asteroid being developed by Newcastle University.

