### Eligibility criteria

These are summarised in Table 1.

**Table 1 Tab1:** Table of inclusion and exclusion criteria for the three groups in the clinical trial

Group 1	Group 2	Group 3
Anisometropic amblyopia	Strabismic or mixed amblyopia	Post-strabismus surgery
Inclusion criteria		
3.5^5^–12^4^ years	3.5^5^–12^4^ years	3.5^5^–12^4^
Vision in amblyopic eye between 0.3 and 1.3 logMAR with an intraocular difference of 0.2 logMAR or more	Vision in amblyopic eye between 0.3 and 1.3 logMAR with an intraocular difference of 0.2 logMAR or more	Vision in amblyopic eye between 0.3 and 1.3 logMAR with an intraocular difference of 0.2 logMAR or more
May have a manifest squint of less than or equal to 10 prism dioptres	Manifest squint must be greater than 10 prism dioptres	Residual squint following surgery (no more than 4 weeks prior) of any size
Undergone refractive adaptation^1^	Undergone refractive adaptation (if indicated)^1,2^	Undergone refractive adaptation (if indicated) ^1,2^
No previous patching or penalisation	Previous patching or penalisation acceptable	Previous patching or penalisation acceptable
No previous strabismus surgery	No previous strabismus surgery	Treatment to start within 4 weeks of strabismus surgery but no previous strabismus surgery
Can use I-BiT Plus	Can use I-BiT Plus	Can use I-BiT Plus
Exclusion criteria		
Deprivational amblyopia		
Presence of manifest nystagmus		
Other ocular or neurological disease affecting the visual system^3^		
Parent, guardian or child not prepared to give consent		

^1^Refractive adaptation is wearing refractive correction for a minimum of 12 weeks

^2^Refractive adaptation is indicated if there is a significant refractive error

^3^These include Down’s syndrome, developmental delay, craniofacial syndrome, foetal alcohol syndrome and cerebral palsy among other conditions

^4^The upper limit of the age range is 1 day before their 13th birthday

^5^The lower limit of the age range is 182 days after their third birthday

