### Sample size

This is a pilot study and, therefore, formal sample size estimations have not been performed.

Based on 20 treated patients per arm, the minimum importance difference of 0.1 logMAR in visual acuity between the I-BiT Plus arm and standard care arm can be observed at 5% significant level with 80% power if the standard deviation is 0.15 logMAR or less. We do not have an accurate estimate of the standard deviation and a known unknown is the compliance rate (both with the treatment and with the trial procedures). The standard deviation in visual acuity at 6 weeks will be estimated to inform sample size calculations for the future trial which will assess clinical effectiveness of the I-BiT™ system.

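### The acuity scoring rule has the wrong sign for logMAR: each error improves the score behind the primary clinical endpoint

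*Protocol article*

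**What the plan says.** Three statements in the Baseline assessments section make up the rule. Testing "terminates when the participant fails to correctly score 3 out of 4 on a line". The base value follows: "The vision is scored as the line that the tested was completed on". Then comes the adjustment: "0.025 is subtracted for every error made on that line and on the preceding line". The permitted charts are "Keeler LogMAR crowded, crowded LogMAR Kays pictures or the Bailey-Lovie LogMAR test", so every score is in logMAR.

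The direction of the scale is clear from Table 1 under Eligibility criteria, which requires "Vision in amblyopic eye between 0.3 and 1.3 logMAR with an intraocular difference of 0.2 logMAR or more". The amblyopic eye is the eye with reduced acuity, so larger values mean poorer vision.

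No other section gives a different rule or an inverted scale. The Discussion says the method was agreed through a Delphi-like process because the four centres had applied the tests differently, and that consistency was stressed to them.

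**The concern.** On a scale where higher is worse, a misread optotype should raise the score. The printed rule lowers it. Among children who stop on the same line, the one who reads fewest optotypes gets the best acuity, and a real gain within a line is recorded as a loss.

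This score has four uses in the trial:

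- the primary clinical endpoint, change from baseline to week 6 (Primary outcome);
- the baseline covariate in the ANCOVA (Statistical methods);
- the eligibility value (Table 1);
- the source of the SD that the Sample size section wants for planning the definitive trial.

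The rule is also the means of standardising four centres. If some sites follow it literally and others silently correct it, their scores are not comparable.

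**Working it through.** **Inputs from the article.** Four optotypes per line; stop when fewer than three are read correctly; adjustment of 0.025 per error on two lines (all Baseline assessments). Minimum important difference 0.1 logMAR, 20 per arm, SD 0.15 (Sample size). **Assumed, not in the article:** lines 0.1 logMAR apart.

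**1. The step size.** 0.1 / 4 = 0.025. The plan's figure reproduces, so only the sign is in question.

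**2. All error patterns, base value taken as the line where testing stopped (L = 0.40).** The stopping line carries 2 to 4 errors. The line before it was passed, so it carries 0 or 1. With e total errors, the printed score is L − 0.025e, the score with errors added is L + 0.025e, and the gap is 0.05e.

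| Errors on stopping line | Errors on line before | As printed | Errors added | Gap |
|---|---|---|---|---|
| 2 | 0 | 0.350 | 0.450 | 0.10 |
| 2 | 1 | 0.325 | 0.475 | 0.15 |
| 3 | 0 | 0.325 | 0.475 | 0.15 |
| 3 | 1 | 0.300 | 0.500 | 0.20 |
| 4 | 0 | 0.300 | 0.500 | 0.20 |
| 4 | 1 | 0.275 | 0.525 | 0.25 |

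The fifth row is a useful check. This child read all of the 0.5 line and none of the 0.4 line. Adding errors gives 0.500, the last line actually read. The printed rule gives 0.300, a line beyond the one the child failed completely.

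**3. The other reading, base value taken as the last line passed (0.50).** That line and the one before it each carry 0 or 1 errors. For e = 0, 1, 2 the printed rule gives 0.500, 0.475, 0.450; adding gives 0.500, 0.525, 0.550. The sign is wrong here too, with smaller consequences.

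**4. Effect on a change score (stopping-line reading).** The error in a change is 0.05 × (difference in error counts between visits). With e from 2 to 5 this reaches 0.05 × 3 = 0.15 logMAR for an individual child.

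**5. Simulation.** Further assumptions: logistic psychometric curve with scale 0.03 to 0.06 logMAR, 5% guessing, and the article's stopping rule.

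| Quantity | Stopping-line reading | Last-passed-line reading |
|---|---|---|
| Mean level: printed rule better by | 0.16 to 0.17 | 0.02 to 0.035 |
| SD of change, scale 0.03: added / printed | 0.045 / 0.089 to 0.091 | 0.053 / 0.072 |
| SD of change, scale 0.06: added / printed | 0.077 / 0.117 | 0.083 / 0.108 |

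Under the stopping-line reading, ignoring errors altogether gives SDs of 0.060 and 0.093, so the printed adjustment is noisier than no adjustment. A true gain of 0.10 is recorded as about 0.10 on average under either sign.

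**6. Effect on power (illustrative).** Suppose 0.15 is the SD of change under correct scoring. The SD under the printed rule is then √(0.15² − s_add² + s_sub²):

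- scale 0.03: √(0.0225 − 0.045² + 0.091²) = 0.170
- scale 0.06: √(0.0225 − 0.077² + 0.117²) = 0.174

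Two-sided t-test power for a difference of 0.1 with 20 per arm is 54% at SD 0.15, 44% at 0.170 and 43% at 0.174. Under the last-passed-line reading the SD is about 0.158 to 0.165 and power about 50% to 46%.

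The start is 54%, not the plan's 80%, because an unadjusted comparison does not reproduce that claim. It would need a baseline correlation of about 0.66 in the ANCOVA, which the article does not state. That is a separate matter; the 54% serves here only as a reference.

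**The case against.** The strongest reply is that the sign is a slip of the pen with little effect on the trial's conclusion.

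- **Change, not level.** The endpoint is change, the rule applies to both arms, assessors are masked, and a true 0.10 gain is still recorded as about 0.10. This stands. The defect should not be described as favouring an arm, and a level gap of 0.15 at one visit is not an error of 0.15 in the treatment effect.
- **Size depends on the reading.** If the base is the last line passed, the level shift is only 0.02 to 0.035 and the loss of power is smaller. This also stands. However, the stopping-line reading is the more natural one, because errors on that line and the one before then capture nearly all errors. The direction is wrong either way.
- **Power figures rest on assumptions.** The line spacing, slope and guessing rate are not in the article, the analysis is ANCOVA rather than a t-test, and the article admits it has no accurate SD and may be underpowered. Fair: the power figures are illustrative.
- **Eligibility.** The 0.2 interocular difference uses two eyes scored the same way, so the average shift largely cancels and mainly noise remains. At the 0.3 limit, scores that are too good make entry stricter, not looser. Both points are right and set the direction of the effect; they do not remove it.
- **Sites may score correctly.** Possible, but nothing in the article shows it, and this is an explicit rule, not a detail left to the full protocol.

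**Conclusion.** The rule is wrong as printed and must be corrected. The sign error follows from the article's own text under either reading of the base line and needs no outside assumption.

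Its size does need assumptions. With 0.1 line spacing and the stopping-line reading, recorded acuity is too good by 0.10 to 0.25 logMAR at a visit. Under the simulated slopes, the measurement SD of change is about 1.5 to 2 times what it should be (0.117/0.077 and 0.091/0.045). The last-passed-line reading gives the same direction with less effect.

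The consequences are extra noise in the primary clinical endpoint and in the baseline covariate, a shifted level at the 0.3 and 1.3 entry limits, and an inflated SD passed on to the definitive trial. Systematic bias in the mean treatment difference is not shown. Whether any recorded data are affected depends on site practice, which the article does not reveal.

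**What to change.** Replace the scoring sentence with, for example: *Record the logMAR value of the line at which testing stopped, then add 0.025 for each optotype misread there or on the line immediately before it.* This reverses the sign and also settles which line is the base value.

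Then:

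1. Compare the wording in the full protocol, the case report forms and the site instructions, and ask each of the four centres how it has scored.
2. If any site subtracted, recompute scores for children already enrolled (34 at April 2018, per Trial status) from the recorded lines and errors, and re-check their eligibility values. This is possible only if lines and error counts were kept in source records, which the article does not say; where they were not, report that limitation.
3. Estimate the SD for the definitive trial from correctly scored data only.

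The cost is a one-sentence amendment and a site memo, plus arithmetic re-scoring if the rule was applied literally. No new visits or measurements are needed.

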### Randomisation and codebreaking

Patients will be assigned sequentially, as each one consents to the clinical investigation, into the I-BiT Plus or control arms using the Simon and Pocock minimisation method (with an 80% chance of attempting to balance) in order to achieve a 1:1 ratio. The minimisation will be stratified by the recruitment centre, age (3.5 – < 6, 6 – < 9 and 9–12 years as the treatment response – visual acuity – is strongly age dependant over this age range for conventional treatment) and history of previous treatment (Yes/No).

The randomisation sequence was generated by the Derby Trials Unit.

The treatment allocation will be done using a web-based randomisation system and undertaken by the research orthoptist at the baseline visit.

It is not possible to mask the intervention and so there is no requirement for code breaking.

### Subsequent assessment

Participants will be assessed at weeks 3 and 6. Those who are randomised to the active treatment will also be assessed at week 10.

### Week-3 assessment

The week-3 visit will include visual acuity measurement, angle of strabismus and binocular vision status.

### Week-6 assessment

The week-6 visit will include visual acuity measurement, angle of strabismus and binocular vision status. Their quality of life will be checked using the CHU-9D and the CATQoL.

On completion of the 6 weeks, the equipment is retrieved from the participant’s home. The machine records how often and for how long it was used and this data is downloaded to a pen drive and separately analysed to determine compliance. The machine’s database is then cleaned prior to reuse.

### Week-10 assessment

The week-10 visit will include visual acuity measurement, angle of strabismus and binocular vision status.

Costs from an NHS and Personal Social Services perspective will be collected by combining recorded activity (caregiver questionnaires) with the appropriate unit cost. Intervention costs including I-BiT system and usual care, and any other relevant NHS resource utilisation within the duration of the trial will also be collected.

### Permitted and prohibited other interventions

Participants may not have patching or penalisation while participating in the trial. Otherwise treatment of other medical conditions is permitted.

### Masking

It is not possible to mask the intervention (as can be readily determined by the participant shutting their amblyopic eye). The clinical assessments are performed by an orthoptist masked to the intervention and the participant and parent instructed not to inform the assessing orthoptist. A record is kept of which orthoptist(s) are aware of the treatment allocation and is updated should the allocation get revealed to a particular individual.

### Outcomes

#### Primary outcome

There are two primary endpoints for the trial arms:Feasibility will be assessed by the number of hours of treatment deliveredThe primary clinical endpoint will be the change of visual acuity from baseline to week 6 post receipt of the I-BiT Plus or laptop between the two arms in each group

#### Secondary outcomes

The secondary outcomes for feasibility will include: recruitment rate and reasons for not taking part, treatment times and the proportion of patients completing a course of treatment (defined as 18 or more hours, which is 30 min per day, 6 days per week for 6 weeks), equipment breakages, retention rates and reasons for drop out, problems encountered with the randomisation process, completeness of outcome data and analysis of protocol deviations to determine rates and causes of non-compliance.

The secondary clinical out measures will include:Changes in visual acuityChanges in binocular status and includes stereoacuityChanges in angle of strabismusQuality of life outcomes

### Safety assessment

All adverse events will be recorded and categorised according to whether they are device related. Anticipated adverse events include headache, nausea, double vision, reverse amblyopia and photosensitive epilepsy.

The previous I-BiT trial did report two cases of diplopia were considered adverse device (I-BiT) [14] events which resolved on stopping treatment, while in the PEDIG trial the incidence was both low and considered similar in the dichoptic and the patched arms [17]. Reverse amblyopia and photosensitive epilepsy have not been reported.

Double vision may occur as part of the treatment process as breaking suppression may be necessary prior to developing fusion. It is left to the judgement of the site’s principle investigator as to whether it is appropriate for any participant who develops this, or any other adverse event, to remain in the trial or to be withdrawn.

Participants are covered by NHS indemnity.

### Sample size

This is a pilot study and, therefore, formal sample size estimations have not been performed.

Based on 20 treated patients per arm, the minimum importance difference of 0.1 logMAR in visual acuity between the I-BiT Plus arm and standard care arm can be observed at 5% significant level with 80% power if the standard deviation is 0.15 logMAR or less. We do not have an accurate estimate of the standard deviation and a known unknown is the compliance rate (both with the treatment and with the trial procedures). The standard deviation in visual acuity at 6 weeks will be estimated to inform sample size calculations for the future trial which will assess clinical effectiveness of the I-BiT™ system.

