### Trial design

The trial protocol is version 1.4 and dated 19 December 2016. The trial is a single-masked, randomised control trial. It is not possible to mask the intervention as the participant has only to shut one eye to know whether they are in the treatment or the control arm.

The trial is split into three groups each of these three groups will investigate a distinct (and mutually exclusive) patient population which together cover most cases of anisometropic or strabismic amblyopia that presents to the National Health Service:Group 1: untreated anisometropic amblyopia.Group 2: strabismic or mixed amblyopia with no previous strabismus surgery (but may have had previous amblyopia treatment)Group 3: immediate post-strabismus surgery. Participants with residual strabismic or mixed amblyopia undergoing alignment surgery. These participants will receive I-BiT Plus treatment starting in the immediate post-operative period

The trial will be assessor masked (it is not possible to mask the intervention) randomised intervention with 40 participants in each group with either continued refractive adaptation (if glasses are indicated and prescribed) or observation as the controls. The participants in the control arm will also be provided with a gaming computer on which they can play games and watch DVDs but will not have the capability to provide dichoptic stimulation nor provide eye-tracking. Carers will be provided with a contact number for enquiries and technical help.

In all three groups, the participants will be randomised to either receive I-BiT Plus for 6 weeks or extended refractive adaptation/observation and will be examined at weeks 3 and 6 post receipt of I-BiT Plus or laptop for both arms, and at week 10 in the I-BiT treatment arm only. In all three groups, after week 6, the participants in the control arms will be returned to standard NHS care while the intervention arms will be observed for a further 4 weeks. The rationale is that the week-6 visit is the comparison between treated and controls and is the primary endpoint. The point of the week 10 visit is to see if any improvement observed in the treated arm is stable or not and the comparison is, therefore, between the week-6 and the week-10 visits for the treated arms.

The choice of untreated controls was chosen as the most suitable choice for determining whether I-BiT is an effective treatment and superior to no treatment.

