## Discussion

This is a randomised controlled trial for the revised I-BiT™ system. There is now a body of evidence that dichoptic stimulation is an effective treatment for amblyopia [9] and this trial builds on previous work [13, 14, 19]. We have used the lessons from the previous studies to redesign the I-BiT system with the following improvements:Home-based system. Simple to use and also safe. For example, it will switch itself off if it is left idle for 15 min. The current system is designed to be used without supervisionRange of games and videos (as opposed to one game and one video)Allow image off-setting for strabismic and mixed amblyopiaSimple psychophysical tests incorporatedMonitor activities undertaken and treatment time. It will not permit a treatment session to be longer than 1 h or more than 2 h in 1 dayWe also included a face verification system to help ensure that the person using the system is the intended participant

The major aim of this trial is as a feasibility study to see if all these features function as designed and at the same time get some indication of efficiency. The intention is to get sufficient information to allow a definitive study to be designed.

It should be noted that this approach is not without its problems. A major cause of treatment failure with patching is poor compliance [7, 20] but videogames must be engaging and can have their own compliance issues. In the PEDIG study, only 22% of participants complied with more than 75% of the prescribed treatment. The revised I-BiT has programmed up eight games in an attempt to ensure a reasonable choice and includes around 40 h of videos which are particularly targeted to the 3.5–6 years age range where they may be less inclined to the gaming options.

It is the issue of compliance that undermines any power calculation. We are just powered to detect a clinically significant difference but this is assuming good compliance. So it is likely that we will end up under powered, but we will have a measure of compliance which can be used for future calculations.

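### The stated 80% power does not follow from its inputs: 20 per arm with SD 0.15 gives about 54% power for a 0.1 logMAR difference between arms

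*Protocol article*

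**What the plan says.** The Sample size section calls the trial a pilot without a formal sample size estimation, then gives a power statement. The arm size is "Based on 20 treated patients per arm". The target is a "minimum importance difference of 0.1 logMAR in visual acuity between the I-BiT Plus arm and standard care arm". This, it says, "can be observed at 5% significant level with 80% power if the standard deviation is 0.15 logMAR or less". It adds that the SD is not accurately known and that compliance is unknown.

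The Trial design section describes a "randomised intervention with 40 participants in each group", and Randomisation and codebreaking allocates "in order to achieve a 1:1 ratio". Statistical methods analyses the three groups separately by ANCOVA, adjusting for baseline acuity, age and centre, at the 0.05 level and with 95% confidence intervals. Change in acuity to week 6 between arms is one of the two primary endpoints (Primary outcome).

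The Discussion returns to power: "We are just powered to detect a clinically significant difference but this is assuming good compliance". It goes on to expect that the trial will probably end up underpowered, and gives compliance as the reason.

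**The concern.** The power sentence is about a difference between two arms of 20, but 80% is far higher than such a comparison gives when the difference is two-thirds of an SD. It is close to what a single sample of 20 would give. If so, the plan overstates the power for a primary endpoint in all three groups.

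Two things follow. A non-significant result in a group could be taken as evidence against a clinically important effect, or put down to poor compliance, when ordinary sampling error would explain it. The trial is also meant to supply the SD for the sample size of a definitive study; the same arithmetic carried forward would make that study too small.

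**Working it through.** **Inputs.** From the Sample size section: n = 20 per arm, difference δ = 0.1 logMAR, SD σ = 0.15, 5% level. The 20 agrees with 40 per group allocated 1:1. The article does not state sidedness. I take two-sided, which fits the planned 95% intervals, and also show one-sided. Powers are from the noncentral t distribution. The standardised difference is d = 0.1/0.15 = 0.667.

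**Trying to reproduce the stated 80%**

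- Two-sample test: noncentrality = δ/(σ√(2/n)) = 0.1/(0.15 × √0.1) = 0.1/0.0474 = 2.108, with 38 degrees of freedom. Two-sided power is **53.8%** (normal approximation 55.9%). One-sided power is 66.5% (normal approximation 67.8%).
- 40 per arm, in case group size was taken for arm size: 83.8%. This does not match.
- One-sample or paired test, n = 20: noncentrality = δ/(σ/√n) = 0.1/(0.15/√20) = 2.981, with 19 degrees of freedom. Two-sided power is **80.7%**. With n = 19 it is 78.5%, so 20 is the smallest sample that reaches 80%. The largest SD that gives 80% at n = 20 is 0.151, which agrees with the stated limit of 0.15.

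Of these calculations only the one-sample one returns the plan's figures.

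**What 80% would need in the two-sample comparison (two-sided 5%)**

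- At 20 per arm the detectable standardised difference is d = 0.909. The SD must then be at most 0.1/0.909 = 0.110, or the true difference at least 0.909 × 0.15 = 0.136 logMAR.
- At SD 0.15 and δ = 0.1, the solution is n = 36.3, so 37 per arm (36 gives 79.7%).

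**Precision.** The expected half-width of the 95% interval is t(0.975; 38) × σ√(2/n) = 2.024 × 0.15 × √0.1 = 0.096 logMAR, almost the whole minimum important difference.

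**Loss to follow-up (illustrative).** The article gives no allowance. If 10% were lost, as in the earlier pilot where nine of 10 completed, 18 per arm would give 49%.

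**ANCOVA.** The article does not define which SD the 0.15 is. The powers below ignore the few degrees of freedom spent on covariates.

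- *Unadjusted week-6 SD.* Residual SD = 0.15√(1 − r²), where r is the correlation of baseline with week 6.

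| r | Residual SD | Power |
|---|---|---|
| 0.5 | 0.130 | 66% |
| 0.6 | 0.120 | 73% |
| 0.68 | 0.110 | 80% |
| 0.7 | 0.107 | 82% |
| 0.8 | 0.090 | 93% |

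- *SD of change.* With equal variances at both visits, residual SD = 0.15√((1 + r)/2). Power is 66% at r = 0.5, 61% at r = 0.7 and 58% at r = 0.8. It reaches 80% only if r is below about 0.08.
- *Residual SD.* Power stays at 54%.

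**The case against.** The strongest defence is that the trial presents itself as a feasibility study. It disclaims a formal sample size, defers clinical effectiveness to a later trial, promises effect sizes with confidence intervals, and says that it will probably be underpowered. The Sample size section also names the unknown SD, not only compliance. On this view the power sentence is an aside and a correction changes neither the patients nor the analysis. This stands as a limit on the consequences. It does not make the published number right, and the Discussion relies on that number. Neither caveat tells the reader that power is near 54% at the stated SD even with full compliance and no loss.

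The second defence is ANCOVA. The section's last sentence speaks of the SD of acuity at 6 weeks, so reading 0.15 as the unadjusted SD is reasonable, and a strong baseline correlation could then bring power to 80% or more. This also stands as a condition: the 54% holds for the comparison as the sentence describes it, and the true figure depends on which SD is meant. But the sentence mentions neither adjustment nor a correlation, so it does not support 80%.

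Finally, the one-sample origin is an inference from the match. The finding does not depend on it.

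**Conclusion.** The concern holds. On the plan's own inputs, power for a 0.1 logMAR difference between arms is about 54% two-sided, not 80%, an overstatement of about 26 points. A true effect of that size would be missed in about 46% of trials (100 − 53.8), with perfect compliance and no loss. A one-sided test does not close the gap.

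The 54% assumes 20 analysed per arm and that 0.15 is the SD that applies to the comparison. If 0.15 is the unadjusted week-6 SD, power rises with the baseline correlation and reaches 80% at about r = 0.68, a value the article neither states nor supports. The Discussion's claim of being only just powered carries the error forward and attributes the expected shortfall to compliance when the arm size is already enough to explain it.

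**What to change.** 1. In Sample size, replace the power statement with wording such as: *With 20 analysed per arm in each group and a residual SD of 0.15 logMAR, a two-sided 5% test has about 54% power for a between-arm difference of 0.1 logMAR. Power of 80% would need a residual SD of about 0.11 or a difference of about 0.136. The expected half-width of the 95% confidence interval is about 0.10 logMAR.*
2. Say which SD the 0.15 is. If the authors intended the gain from baseline adjustment, state the assumed correlation and its source, and give power over a range of values.
3. In the Discussion, delete the sentence "We are just powered to detect a clinically significant difference but this is assuming good compliance" and say that the arm size itself limits power, with compliance and loss reducing it further.
4. State that a non-significant result in a group does not exclude a 0.1 logMAR benefit and that the confidence interval should carry the interpretation.

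The cost is wording only: no extra patients and no change to endpoint or analysis. The stated power becomes less favourable.
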